## 14.2 SAMPLE SIZE AND ACCRUAL

The primary aim of the study is to assess the local and systemic safety of one and seven day exposures to MB66. The primary endpoint is the proportion of participants who experience a Grade 2 or higher adverse event (AE) deemed related to study product. (The proposed total sample size is N=38 evaluable participants divided into Segment A (with n = 8 evaluable), and Segment B (with two arms, a MB66 arm and a placebo film arm, each with n = 15 evaluable). Evaluable participants (evaluable for the primary endpoint) in Segment A will be defined as participants who complete the Screening and Enrollment Visits and return for Visit 3. Evaluable participants in Segment B will be defined as participants who complete the Screening and Enrollment Visits and return for Visit 4 and use study product for at least 5 of the previous 7 days including the day before presentation (as assessed with MEMS cap data). Non-evaluable participants will be replaced, however, their data relevant to endpoints other than the primary endpoint will be preserved and used in tabulation and analysis of secondary and exploratory endpoints. In addition, if a participant becomes non-evaluable prior to the predefined visits described above, but experiences an AE during the time they were on study, their data will be included in the primary analyses as well. Based on previous studies of vaginal products conducted at the study site, the accrual of 38 evaluable subjects with normal reproductive tracts is expected to require the screening of approximately 70 participants and the enrollment of approximately 43 participants. The target for retention will be approximately 90% of enrolled participants over the 7-14-day follow-up period. Therefore, it is anticipated that 23 women exposed to active study drug in all arms (8 during Segment A and 15 during Segment B) will be evaluable. [Table 16](#) calculates the probability of events in Segment A participants (n=8) and [Table 17](#) calculates the probability of events in Segment B participants (n=15).

**Table 16: Exact Binomial probabilities for different scenarios for Segment A (n=8) for Study MB66-01**

| Event Rate | P
(No events   n=8) | P
(1 event   n=8) | P
(2 or more events   n=8) |
|------------|------------------------|----------------------|-------------------------------|
| 1%         | 0.92                   | 0.07                 | 0.000054                      |
| 5%         | 0.66                   | 0.28                 | 0.057                         |
| 10%        | 0.43                   | 0.38                 | 0.19                          |
| 15%        | 0.27                   | 0.38                 | 0.34                          |
| 20%        | 0.17                   | 0.34                 | 0.50                          |
| 25%        | 0.10                   | 0.27                 | 0.63                          |
| 30%        | 0.058                  | 0.20                 | 0.74                          |

|     |        |       |      |
|-----|--------|-------|------|
| 35% | 0.032  | 0.14  | 0.83 |
| 40% | 0.017  | 0.09  | 0.89 |
| 45% | 0.0084 | 0.055 | 0.94 |
| 50% | 0.0039 | 0.031 | 0.96 |

**Table 17: Exact Binomial probabilities for different scenarios for Segment B (n=15) for Study MB66-01**

| Event Rate | P
(No events   n=15) | P
(1 event   n=15) | P
(2 or more events   n=15) |
|-------------------|---------------------------------|-------------------------------|----------------------------------------|
| 1%                | 0.86                            | 0.13                          | 0.01                                   |
| 5%                | 0.46                            | 0.37                          | 0.17                                   |
| 10%               | 0.21                            | 0.34                          | 0.45                                   |
| 15%               | 0.09                            | 0.23                          | 0.62                                   |
| 20%               | 0.04                            | 0.13                          | 0.83                                   |
| 25%               | 0.0134                          | 0.067                         | 0.92                                   |
| 30%               | 0.005                           | 0.03                          | 0.965                                  |

The sample size for Segment A is large enough to rule out 50% Grade 2 or higher adverse rate with n=8 patients. With 8 participants in this segment a one-sided 95% Clopper-Pearson (exact) binomial confidence interval will have an upper limit of 47% if one out of eight women has a Grade 2 (or higher) adverse event (AE2) related to the study product. Furthermore, the sample size for Segment B was chosen to have an adequate sample size to rule out 30% grade 2 or higher adverse event rate for each of the groups. With 15 participants in an arm a one-sided 95% Clopper-Pearson (exact) binomial confidence interval will have an upper limit of 27.9% if one out of 15 women has an AE2 related to the study product.

In addition to estimating the rate of Grade 2 (or higher) AE's in Segment B alone, estimates of combined AE2 rates can be derived by pooling the participants from Segment A and Segment B. Segment A participants (n=8) can be pooled with the participants from Segment B, allowing for AE2 estimates to be made using n=23 participants. One-sided 95% Clopper-Pearson (exact) binomial confidence intervals will be estimated for these AE2 rates. For the analyses with n=23 participants, the confidence intervals will have an upper bound of 29.4% if 2 (or fewer) participants have an AE2. These analyses will provide supportive data to the primary endpoint analysis that is based on the Segment B (n=15) participants only.

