AE2's will be estimated for each group. The focus of these analyses will be to determine whether a 30% AE2 rate can be ruled out based on the data collected in the study. This will be shown if the upper bound of the 1-sided 95% Clopper Pearson (exact) binomial confidence interval is less than 30% which will occur if zero or one participant out of the 15 enrolled (in each arm) have an AE2. In addition, an exploratory comparison between the two groups in Segment B (active and vehicle) will be performed using a Fisher's Exact test to determine whether the number of participants with Grade 2 or higher AEs are different between groups. In addition to estimating the rate of Grade 2 (or higher) AE's in Segment B alone, estimates of combined Grade 2 or higher AEs rates can be derived by pooling the participants from Segment A and Segment B. In addition, Segment A participants (n=8) can be pooled with the participants from Segment B, allowing for Grade 2 or higher AEs estimates to be made using n=23 participants. One-sided 95% Clopper-Pearson (exact) binomial confidence intervals will be estimated for these AE2 rates. For the analyses with n=23 participants, the confidence intervals will have an upper bound of 29.4% if 2 (or fewer) participants have an Grade 2 or higher AEs. These analyses will provide supportive data to the primary endpoint analysis that is based on the Segment B (n=15) participants only. Additional detail of the statistical analyses will be provided in a separate statistical analysis plan (SAP), which will be prepared and signed off prior to completion of the study.

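### The 29.4% upper bound stated for 2 events in the pooled n=23 analysis should be 24.9%, and one cell in each of Tables 16 and 17 is wrong; the Segment B rule is unaffected

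*Protocol*

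**What the plan says.** Section 14.2 of the protocol gives three exact upper bounds for the rate of related Grade 2 or higher adverse events (AE2). For Segment A (n=8) the interval "will have an upper limit of 47% if one out of eight women has a Grade 2 (or higher) adverse event (AE2". For a Segment B arm (n=15) it "will have an upper limit of 27.9% if one out of 15 women has an AE2 related to the study product". Segment A may then be pooled with Segment B, "allowing for AE2 estimates to be made using n=23 participants". The method for the pool is explicit: "One-sided 95% Clopper-Pearson (exact) binomial confidence intervals will be estimated for these AE2 rates". The result is stated as "the confidence intervals will have an upper bound of 29.4% if 2 (or fewer) participants have an AE2".

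Section 14.7.2, the primary endpoint analysis, repeats it: "the confidence intervals will have an upper bound of 29.4% if 2 (or fewer) participants have an Grade 2 or higher AEs". The aim of the Segment B analysis in that section is to "determine whether a 30% AE2 rate can be ruled out based on the data collected in the study". This is met when the upper bound is below 30%, that is, with zero or one AE2 among 15. Both sections call the pooled analysis supportive and base the primary analysis on the 15 Segment B participants.

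Tables 16 and 17 list the exact binomial probabilities of 0, 1, and 2 or more events for n=8 and n=15 over a range of true rates. Table 16, 1% row, prints 0.92, 0.07 and 0.000054. Table 17, 15% row, prints 0.09, 0.23 and 0.62.

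**The concern.** Method, sidedness, level, count and sample size are all given, so the pooled bound can be checked directly, and it does not reproduce. It sits just under the 30% benchmark and appears in the primary analysis section, where it could be copied into later documents.

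Table 17 matters a little more than an illustration would. With 15 women, two or more events is exactly the outcome in which an arm fails to rule out 30%, so the last column is the failure probability of the rule. A reader judging how demanding the rule is at a true rate of 15% takes the wrong number from that cell. The Table 16 cell is wrong by a large factor but is very small either way.

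**Working it through.** **Inputs.** One-sided 95% Clopper-Pearson; n = 8, 15 and 23 = 8 + 15; 2 events in the pool; benchmark 30%. All are from Sections 14.2 and 14.7.2.

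**Formula.** With x events in n women, the upper limit U solves P(X ≤ x | n, U) = 0.05, which gives U = Beta quantile(0.95; x+1, n−x).

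**The protocol's other bounds first.**

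| Events / n | Beta quantile | Result | Protocol |
|---|---|---|---|
| 1/8 | (0.95; 2, 7) | 47.07% | 47% |
| 1/15 | (0.95; 2, 14) | 27.94% | 27.9% |

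Both reproduce, so the method is correctly identified.

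**Pooled n=23.**

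| Events / n | Beta quantile | Result | Protocol |
|---|---|---|---|
| 0/23 | (0.95; 1, 23) | 12.2% | – |
| 1/23 | (0.95; 2, 22) | 19.0% | – |
| 2/23 | (0.95; 3, 21) | 24.9% | 29.4% |
| 3/23 | (0.95; 4, 20) | 30.4% | – |

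Direct check at U = 0.2492: P(0) + P(1) + P(2) = 0.0014 + 0.0105 + 0.0382 = 0.050, as required. At U = 0.294: 0.0003 + 0.0032 + 0.0146 = 0.018, so 29.4% is not the 95% limit. The discrepancy is 29.4 − 24.9 = 4.5 points.

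**Could another convention explain it?** For 2/23 the two-sided 95% Clopper-Pearson limit is 28.0%, the one-sided 99% limit 31.8% and the one-sided 90% limit 21.5%. Wilson, Agresti-Coull, Jeffreys, Wald and inverted-test limits, at two-sided 90% and 95%, lie between 18.4% and 28.0%. None of these gives 29.4%.

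**Table 16, 1% row, n=8.**
- P(0) = 0.99^8 = 0.9227
- P(1) = 8 × 0.01 × 0.99^7 = 0.0746
- P(2 or more) = 1 − 0.9227 − 0.0746 = 0.0027

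The printed 0.000054 equals P(3 or more). The ratio is 0.00269 / 0.000054, about 50; the absolute difference is about 0.0026.

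**Table 17, 15% row, n=15.**
- P(0) = 0.85^15 = 0.0874
- P(1) = 15 × 0.15 × 0.85^14 = 0.2312
- P(2 or more) = 1 − 0.0874 − 0.2312 = 0.6814

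The printed row sums to 0.09 + 0.23 + 0.62 = 0.94, too far from 1 for rounding. All other cells in both tables agree with the exact values within rounding.

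**Link to the Segment B rule.** The bounds for 0, 1 and 2 of 15 are 18.1%, 27.9% and 36.3%. Only 0 or 1 falls below 30%, so P(2 or more | n=15) is the chance that an arm fails: 0.68 at a true 15% rate, where the table shows 0.62.

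**The case against.** The strongest case on the other side is that nothing depends on these figures, and most of it stands. The primary rule is stated with its correct bound, 27.9% for 1 of 15. The sample sizes are justified by the 47% and 27.9% bounds, and both reproduce. The 29.4% figure errs on the conservative side, since it overstates the upper limit. Both 29.4% and 24.9% lie below 30%, and 3 of 23 gives 30.4%, so 2 is the largest pooled count that excludes 30% under either figure. The intervals will in any case be computed from the data. The correct Table 17 value follows by subtraction from the neighbouring cells. What the objection does not do is make the printed numbers right.

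Three stronger readings are tempting, and the protocol does not support them.

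- A reader might infer that the safety criterion or the sample size is compromised. Neither uses the pooled bound or the two wrong cells.
- A reader might infer that pooling could mask a Segment B failure, because 2 of 15 gives 36.3% while the pooled 2 of 23 gives 24.9%. Sections 14.2 and 14.7.2 both base the primary analysis on the Segment B participants only, so 2 of 15 fails whatever the pool shows. The mix of single-dose and seven-dose women is stated openly.
- A reader might take the 50-fold error in Table 16 as a misstated decision rule. Table 16 does not describe the 30% rule. Section 14.2 sets Segment A against a 50% rate, and progression rests on the safety review team's judgement (Section 14.7.2) and the criteria in Section 13.8.

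**Conclusion.** The point holds as a minor correction of three stated figures, one of which is printed twice. The pooled bound is overstated by 4.5 points. The Table 17 cell understates the chance of failing the 30% rule at a true 15% rate by 0.06. The Table 16 cell is about 50 times too small but differs by less than 0.003 in absolute terms. The conclusion takes the interval method as the protocol names it, exactly 23 and 15 analysed participants, and independent events with a common rate within each group, as the binomial tables themselves assume. It does not bear on the Segment B rule, the planned numbers or the status of the pooled analysis.

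**What to change.** In Sections 14.2 and 14.7.2, replace 29.4% with 24.9%, worded as an upper bound of at most 24.9% with 2 or fewer events. Optionally add that 3 of 23 would give 30.4%, so readers can see where the pool stops excluding 30%. In Table 16, 1% row, change the last cell to 0.0027. In Table 17, 15% row, change the last cell to 0.68. If a separate statistical analysis plan carries any of these figures, correct them there too. The cost is text and table edits only, with no change to design, sample size or analysis.

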### 14.3 JUSTIFICATION FOR PLACEBO

This study will utilize a placebo film in Segment B. The placebo control will be a vehicle film containing the same excipients as the active antibody film, and will be administered as one full film in Segment B. Inclusion of a placebo film in this trial will allow investigators to establish the prevalence of adverse events that may be associated with exposure to the film vehicle excipients versus the effect of the MAbs comprising MB66.

The inclusion of a Placebo Group in Segment B also will allow us to rule out large differences in AE2 rates between the Active and Placebo groups. Table 18 below depicts detectable differences and statistical power when comparing Segment B Placebo and Active arms (n=15 per group) for AE2 rates using a Fisher's exact test with  $\alpha=0.05$  (2-sided) for comparisons.

**Table 18: Detectable differences and statistical power**

| AE2 Rate in Active Arm | AE2 Rate in Placebo Arm | Power |
|------------------------|-------------------------|-------|
| 0.001                  | 0.46                    | 88%   |
| 0.067                  | 0.60                    | 83%   |
| 0.13                   | 0.73                    | 88%   |
| 0.2                    | 0.8                     | 87%   |

So for instance, if 1/15 (6.7%) of participants in the Active Arm has an AE2 whereas 9/15 (60%) or more have an AE2 in the Placebo Arm there will be 83% power to detect this difference. It should be noted that this calculation also suggests that if 6.7% of participants in the Placebo Arm had an AE2 and 60% (or more) participants in the Active Arm had an AE2 there would be 83% power to detect that difference as well.

Conversely, our rationale for *not* using a placebo in Segment A (single dose, open label, active film only) is that this preliminary Segment is very small, and is included only to provide a very limited exposure with this first in human use of the MB66 film before going on to the larger Segment B, with a repeated dosing regimen. We acknowledge that there is a risk that without a concurrent vehicle control placebo arm in Segment A, AEs that are due to the film vehicle rather than the mAbs. However, we judge this risk to be very low based on the widespread use of a commercial vaginal film (VCF, Vaginal Contraceptive Film) a PVA-based film with very similar excipients, and the low toxicity of the MB66 vehicle placebo in preclinical animal studies (see Section 6.1.3). For this reason, we believe more will be gained by increasing the number of participants in Segment A receiving active MB66 film than from including a vehicle control placebo arm.

## 14.4 STUDY ENDPOINTS

### 14.4.1 Primary Endpoint: Grade 2 Adverse events

The primary safety endpoint is the clinical or laboratory evidence of a Grade 2 or higher Adverse Event that is judged to be related to study product. Adverse events will be graded according to the following reference: *Division of AIDS (DAIDS) Table for Grading the Severity of Adult and Pediatric Adverse Events, Version 2.0, Nov 2014*, and the Female Genital Grading Table for Use in Microbicide Studies (Addendum 1 to the DAIDS Table for Grading Adult and Pediatric Adverse Events, Version 1.0, November 2007 [Clarification dated August 2009]).

#### **14.4.2 Secondary Endpoints: Pharmacokinetics (PK)**

##### Distribution and Persistence of MB66 MAbs in CVF

The vaginal distribution and persistence of MB66 MAbs, VRC01-N and HSV8-N, will be determined by ELISAs carried out on vaginal fluid collected via Tear Flo strips. The fluid will be collected from different regions of the vagina and at different times after administration.

##### Systemic Absorption of VRC01 and HSV8

Serum samples will be obtained for testing of systemic absorption by ELISA for the VRC01-N Drug Substances. The expected ~50% probability of seropositivity to HSV-1 and/or HSV-2 precludes unambiguous assays for the absorption of the anti herpes Mab (HSV8-N) in participants with preexisting seropositivity, though informative data will be available from HSV seronegatives.

##### Dissolution of Study Film

Visual assessments of the degree of dissolution of study film will be made during speculum exams at intervals after vaginal insertion. The degree of film solubilization (conversion from a solid film to a hydrated gel-like consistency) will be assessed as follows: 100%, between 75 and 100%; between 50 and 75%; between 25 and 50%; between none and 25%; and no evident dissolution.

#### **14.4.3 Exploratory Endpoints**

##### **Ex vivo antiviral effect**

Assays will be done to determine the ex vivo viral neutralization of HIV-1 and HSV-2 in cervicovaginal lavage fluid after MB66 dosing. The endpoint of viral neutralization activity will be determined with ex vivo challenge with HIV-1 and HSV-2 addition to serially diluted CVL fluid. *In vitro* anti-HIV activity will be determined by the TZM-bl assay, and the *in vitro* anti-HSV-2 activity will be assayed by ELVIS HSV Test System, both in [name] laboratory at Boston University School of Medicine.

##### **Cervicovaginal microbial environment**

##### Vaginal pH

Vaginal pH will be measured with pH paper. A change from normal ( $< 4.5$ ) at baseline to  $\geq 4.5$  at Visit 4 will be considered a clinically significant change in vaginal pH.

### Nugent score

The morphotypes of vaginal bacteria will be assessed using Nugent scoring of Gram stained vaginal smears. The Nugent score is graded 1 to 10 as follows:

- 1) Normal, 0-3
- 2) Intermediate, 4-6
- 3) Bacterial Vaginosis, 7-10

### Vaginal microbiome assessment

Becton Dickinson eSwabs will be stored frozen for characterization of the vaginal microbiome before and after study film use by polymerase chain reaction (PCR) to determine the relative proportions of resident vaginal bacteria. Meaningful changes will be defined as a shift from a lactobacillus-dominated community to a mixed community dominated by BV associated bacteria.

### Levels of Immune mediators in Cervicovaginal Lavage

Concentrations of cytokines and other immune mediators will be measured before and after study film exposure.

### **Acceptability**

The acceptability of MB66 film will be assessed by computer administered structured interview (CASI) after 7 days of MB66 or placebo film.

## **14.5 BLINDING**

Segment A will be open label since all participants will receive active film. Segment B participants will be blinded to assignment of active drug versus placebo. Because the active and placebo films are not identical in appearance, study staff cannot reliably be blinded to assignment, and hence we characterize Segment B as “single blind”. However, we will attempt to maintain blinding to assignment during laboratory testing, and among data recording and data analysis teams.

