### 8.1.1 Study Endpoints

#### Primary Endpoint:

Incidence of Grade 2 or higher Adverse Events deemed related to study product, graded according to the *Division of AIDS (DAIDS) Table for Grading the Severity of Adult and Pediatric Adverse Events, Version 2.0, Nov 2014* (Reference 39), and the Female Genital Grading Table for Use in Microbicide Studies (Addendum 1 to the DAIDS Table for Grading Adult and Pediatric Adverse Events, Version 1.0, December 2004 [Clarification dated August 2009]), (see Reference 40). Safety will be assessed throughout the study by monitoring of adverse events, vital signs, physical examinations, and/or clinical laboratory values, and review of concomitant medications and procedures. The number of Grade 2 or higher AEs will be the primary endpoint, but all AEs will be reviewed by the PSRT and analyzed regardless of severity or relationship.

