## 10.3 ADMINISTRATION

A study clinician will manually insert the MB66 film in the clinic for Segment A participants, and Segment B participants will self-administer their first dose of study film in clinic in the presence of the study clinician (to assure themselves and study staff of their ability to insert the film), and then self-administer doses 2-7 at home. Segment B participants will take home their remaining doses in a vial capped with a Medication Event Monitoring System (MEMS) cap, to provide objective data about adherence with and timing of at home dosing, (each opening of the MEMS cap will be electronically recorded for time and date, with data downloaded at Visit 4). An extra dose of study film will be available for each Segment A participant in case of an

initially unsuccessful insertion, and three extra doses provided for each Segment B participant in case of unsuccessful insertion in clinic, at home, or for the possibility of delaying Visit 4 to Day 8 instead of Day 7. *(While the intended duration of exposure for Segment B participants is 7 days, participants who are only able to reschedule Visit 4 on Day 8 post MB66 administration will be allowed to do so. For that group, the total dosing will be 8 days rather than 7. Every effort will be made to bring participants back on Day 7 so as to minimize variation in product exposure. Participants will only be enrolled if they indicate their availability to return on Day 7, but if a scheduling conflict should arise post enrollment, they will be allowed to return to the clinic for Visit 4 on Day 8 after administering an additional dose of film on day 7.)*

For Segment A participants the study will be open label (unmasked). For Segment B, the film identity (active or placebo) will be randomly assigned and assignment will be single blinded (study film identity will be masked to the participants) Reliable blinding of study staff will not be feasible due to the non-identical degree of film translucency of the active and placebo films.

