The PI/designee will grade the severity of each AE and the relationship of the AE to study product:

- AE severity will be graded per the Division of AIDS (DAIDS) Table for Grading the Severity of Adult and Pediatric Adverse Events, Version 2.0. [November 2014], and the Female Genital Grading Table for Use in Microbicide Studies (Addendum 1 to the DAIDS Table for Grading Adult and Pediatric Adverse Events, Version 1.0, November 2007 [Clarification dated August 2009]), except that asymptomatic BV will not be considered an AE. AEs not included in the Female Genital Grading Table for Use in Microbicide Studies mentioned above will be graded by the Division of AIDS (DAIDS) Table for Grading the Severity of Adult and Pediatric Adverse Events, Version 2.0. [November 2014]. In cases where a genital AE is covered in both tables, the Female Genital Grading Table for Use in Microbicide Studies will be the grading scale utilized.
- The relationship of all AEs reported on CRFs will be assessed based on the Manual for Expedited Reporting of Adverse Events to DAIDS, and the clinical judgment of the PI/designee. The study products that must be considered when AE relationships are assigned are MB66 film and placebo film.

The DAIDS Table for Grading Adult and Pediatric Adverse Events, the Female Genital Grading Table for Use in Microbicide Studies, and Version 2.0 of the Manual for Expedited Reporting of Adverse Events to DAIDS are available on the DAIDS Regulatory Support Center (RSC) web site: <http://rsc.tech-res.com/>.

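### The primary endpoint is stated in ways that are not equivalent, and relatedness is judged by staff who cannot reliably be blinded; with 15 women per arm, either can decide the 30% rule

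*Protocol*

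**What the plan says.** **Endpoint.** Section 8.1.1 opens with "Incidence of Grade 2 or higher Adverse Events deemed related to study product". The same paragraph ends differently: "The number of Grade 2 or higher AEs will be the primary endpoint", which is a count of events with no relatedness condition. Section 14.2 says: "The primary endpoint is the proportion of participants who experience a Grade 2 or higher adverse event (AE) deemed related to study product". Section 14.4.1 also requires relatedness. Section 14.7.2 opens with related events, then states the 30% rule in terms of participants with an AE2. It describes the exploratory Fisher test as one "to determine whether the number of participants with Grade 2 or higher AEs are different between groups", without saying whether relatedness applies. Section 14.2 writes out AE2 followed by a separate statement of relatedness, so it is unclear whether the abbreviation alone includes it.

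**Who attributes.** Section 12.1.1: "The PI/designee will grade the severity of each AE and the relationship of the AE to study product".

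**Blinding.** Section 10.3: "Reliable blinding of study staff will not be feasible due to the non-identical degree of film translucency of the active and placebo films". Section 14.5 repeats that "study staff cannot reliably be blinded to assignment", and adds that "we will attempt to maintain blinding to assignment during laboratory testing, and among data recording and data analysis teams". The person who assigns relatedness is not among those teams, and no blinded assessor is named.

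**Decision rule.** In each Segment B arm, the plan asks whether the one-sided 95% Clopper-Pearson upper limit is below 30%. Section 14.7.2 says this needs zero or one participant of 15. Section 14.2 gives 27.9% as the limit at one of 15.

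**The concern.** The three statements differ in two respects: the unit (events or women) and the filter (related or all-cause). They can give different counts from the same data. A Clopper-Pearson interval needs one yes-or-no outcome per woman, so the event count in 8.1.1 cannot feed the planned analysis. The related-or-all-cause question can: both versions are proportions of women, and both could be set against the same 30% rule.

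The filter also rests on a judgement by staff who may be able to tell the films apart. The first hypothesis in section 6.3 is safety compared with placebo. If the between-arm comparison were restricted to related events, it would depend on attributions made without reliable blinding. At stake are the statement that 30% has been ruled out in an arm, and how far the comparison with placebo can be read as randomised evidence.

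**Working it through.** **Inputs.** n = 15 per Segment B arm, one-sided 95% Clopper-Pearson, threshold 30% (sections 14.2 and 14.7.2).

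**1. The plan's own figure.** The upper limit U for x events in n women is the 0.95 quantile of Beta(x + 1, n − x). Equivalently, U solves P(X ≤ x | n, U) = 0.05. For x = 1 and n = 15 this gives 27.94%, which agrees with the stated 27.9%.

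**2. Around the threshold.**

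| Women with an event | Upper limit | 30% ruled out? |
|---|---|---|
| 0/15 | 18.1% | yes |
| 1/15 | 27.9% | yes |
| 2/15 | 36.3% | no |

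The rule turns between 1 and 2.

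**3. Same data, different definitions (constructed example).** Suppose one woman in an arm has a Grade 2 AE judged related and another has a Grade 2 AE judged unrelated.
- Under 14.2 the count is 1/15, the limit is 27.9%, and 30% is ruled out.
- Counting women with any Grade 2 or higher AE gives 2/15, a limit of 36.3%, and 30% is not ruled out.

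If instead one woman has two related Grade 2 AEs, 14.2 gives 1 and the event count in 8.1.1 gives 2. The latter is not a binomial count of women.

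**4. How often the count is at the boundary.** P(X = 1) + P(X = 2) for Binomial(15, p), where p is the assumed true rate of related events:

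| p | P(X = 1) | P(X = 2) | Sum |
|---|---|---|---|
| 5% | 0.366 | 0.135 | 0.50 |
| 10% | 0.343 | 0.267 | 0.61 |
| 15% | 0.231 | 0.286 | 0.52 |
| 20% | 0.132 | 0.231 | 0.36 |

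These sums are ceilings on the chance that one attribution decides the result. At a count of 2, calling one woman's only related event unrelated is enough. At a count of 1, a flip also needs a second woman with a Grade 2 or higher AE that was judged unrelated. At 0, or at 3 or more, a single change does not alter the result.

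**5. How far the definitions can diverge (assumed rates).** Let 30% of women have a Grade 2 or higher AE, and let a fraction r of these women be counted as related. The chance of meeting the rule on the related-only count is P(X ≤ 1 | 15, 0.30r):
- r = 1: rate 30%, chance 0.035
- r = 0.75: rate 22.5%, chance 0.12
- r = 0.5: rate 15%, chance 0.32

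This shows that the two versions estimate different quantities. It is not an estimate of misattribution, because some of those events may truly be unrelated.

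**The case against.** **The inconsistency is loose wording.** Sections 14.2, 14.4.1 and the opening of 14.7.2 all require relatedness, and each stated Clopper-Pearson count is of women or participants. The closing sentence of 8.1.1 goes on to contrast the primary endpoint with a review of all AEs whatever their relationship, which suggests that the related condition was meant to carry over. This is a fair reading, and no Clopper-Pearson interval on an event count is actually planned. But 8.1.1 is the section that defines the endpoints, and what it says there is not what 14.2 says. What the primary endpoint is belongs in the protocol, not among details left to the SAP.

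**The comparison may already be all-cause.** Read literally, the Fisher test in 14.7.2 has no relatedness filter, and it is labelled exploratory. Section 8.1.1 also promises analysis of all AEs. A reader might infer that the planned contrast with placebo is filtered by unblinded attribution; the text does not establish that. It leaves the matter unstated, directly after an endpoint that is restricted to related events.

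**Staff need not know the arm.** A reader might infer that they do. The documents say only that they cannot reliably be blinded. Section 10.4 calls the films similar apart from transparency, and section 10.6 keeps pharmacy records from other research staff. Section 12.1.1 counts placebo film as an investigational product, so a reaction to the vehicle can be judged related in the placebo arm. Neither the direction nor the size of any bias can be derived.

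**The move from 27.9% to 36.3% does not measure harm from unblinding.** A fully blinded judgement would shift the limit by the same amount. This objection stands in full.

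**Segment A is not affected.** It is open label with one arm, so there is no allocation to reveal. Its primary analysis asks whether any related Grade 2 or higher AE occurs, followed by safety-team judgement. The 50% figure in 14.2 justifies the sample size and is not the decision rule.

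**Analysis detail may sit in the SAP.** An all-cause bound or a confidence interval for the difference could be specified there. That bears on where the fix goes; it does not resolve the conflict within the protocol.

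**Conclusion.** The concern holds as a contradiction in the primary endpoint, compounded by an attribution step that is not reliably blinded. Both matter because the Segment B rule turns on one woman: 27.9% at 1/15 against 36.3% at 2/15. Under assumed related-event rates of 5% to 20%, the count falls on 1 or 2 with probability between 0.36 and 0.61. Only then can a single attribution change the result. The documents do not support saying that staff know the arm, that one call always decides, or that bias has been shown. The boundary probabilities assume independent women, exactly 15 per arm and the listed rates. The change is worth making because it is cheap and removes the ambiguity before data are seen.

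**What to change.** 1. Define the primary endpoint throughout as the proportion of participants with at least one related Grade 2 or higher AE. Correct the sentence in 8.1.1 that makes it a number of AEs, and align 14.4.1 and 14.7.2, including whether AE2 implies relatedness.
2. State in 14.7.2 that the Segment B active-placebo comparison uses participants with any Grade 2 or higher AE regardless of relatedness, with a 95% CI for the difference in proportions.
3. In each Segment B arm, report the one-sided 95% upper limit against 30% for all-cause Grade 2 or higher AEs beside the related-only limit.

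**Cost.** Wording and two extra summaries. Section 12.1.1 already has all AEs recorded regardless of severity and presumed relationship, so no visit, participant or data item is added. Background AEs make the all-cause limit less favourable and add noise to the comparison. The same staff also grade severity, so the Grade 1 or Grade 2 call remains unblinded. The fix takes relatedness judgements out of the comparison with placebo; it reduces assessor bias but does not remove it.
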